### Safety Monitoring and Adverse Events

A data and safety monitoring plan was established for the study. On a quarterly basis during the enrollment and data collection period, our research team will review data regarding recruitment, refusals, attrition, differential (study group) attrition, morbidity, and mortality.

Owing to the potential clinical significance of the anxiety and depression data, we will monitor potential anxiety and depression through an evaluation of participants’ T-scores on both the PROMIS-Depression short form 4a and PROMIS-Anxiety short form 4a tools. If a participant has a depression score ≥75.7 (depression) or an anxiety score ≥77.9 (these scores represent the upper 10% in a range of scores), the research assistant will contact the participant via telephone within 48 hours of receiving the score. The research assistant will recommend the participant contact their primary care provider for further evaluation and, in addition, will provide links to the American Psychological Association and State Psychology Associate Therapist databases where they can find names of mental health professionals in their geographic location. This reaction management protocol has been used previously in a large randomized controlled trial that tested this intervention in a cancer caregiver population [31]. All adverse events, concerns, or problems identified by the research team will be reported to the institutional review board and then to the funding agency.

### Data Management

All data will be collected via REDCap and downloaded for use with SPSS and SAS statistical packages. Data management and cleaning involve frequencies for range checks for data values for all variables. Missing data will be examined and imputed as outlined in the PROMIS scoring manual for PROMIS measures. The distress thermometer uses a single item; therefore, cases with missing data for this item will not be included in analyses involving distress. Missing data for other tools will be imputed using mean imputation at the tool level.

### Statistical Methods

Data will be analyzed using SPSS and SAS, and all investigators, along with the statistician and data manager, will have access to the final data set. Before conducting multivariate analyses to examine group differences, we will use descriptive techniques to examine univariate characteristics and bivariate relationships among variables, covariates, and outcomes. These techniques will be based on proportions, medians, and means. We will also describe (for each variable) frequencies and measures of central tendency for all variables and assess data for violations of assumptions for all planned statistical tests. Data transformations will be used to remedy issues concerning nonlinearity or high skewness.

To address the primary outcome (distress), a linear mixed effects model will be used to test whether there is a significant difference between intervention groups in time on the caregiver outcome of distress. The linear mixed effects model will include the variables of group assignment, time, and the interaction of time by group, along with the participant-specific random intercept and slope. Intention-to-treat and per-protocol analyses will be conducted. The linear mixed effects model should be sufficient in most cases to account for missing data in the intention-to-treat analysis. Participants who provide complete data and attend three or more coaching sessions will be included in the per-protocol analysis. We will also explore the influence of COVID-19 anxiety and website usage as covariates and test for moderation by multiple sclerosis disability, race, ethnicity, rural versus urban location of the caregiver, caregiver COVID-19 positive or negative status, whether the caregiver is local or distant from the person with multiple sclerosis, and socioeconomic status. The analytic approach for the secondary outcomes (anxiety, depression, and negative emotions) will be identical to that used for examining the primary outcome of the study.

The study results will be communicated to the participants via email and publication in patient-focused venues, such as the National Multiple Sclerosis Society’s website [78]. In addition, the results will be reported to the sponsor in the final report and via publications and presentations to health care providers in appropriate journals (eg, the *Multiple Sclerosis Journal* and the *Journal of Neurological Sciences*) and conferences.

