## Methods

### Setting

This study takes place virtually using a website designed for the study (delivered to both groups) and coaching via videoconference or telephone (website-coaching group only) to adult caregivers of persons with multiple sclerosis who have responded to recruitment outreach throughout the United States. Trained research assistants will obtain informed consent and collect data remotely using REDCap (Research Electronic Data Capture). REDCap is a secure web application for building and managing web-based surveys and databases for research studies [54].

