**Figure 1 figure1:**
[figure not shown]
Homepage for the “caring for yourself” module from the study website.

Each video vignette (2 to 3 minutes in length) depicts a conversation between a caregiver of a person with multiple sclerosis and another individual (eg, friend, caregiver, or person with multiple sclerosis) discussing an issue identified as relevant during the caregiver engagement process before developing the website. For example, on the website page *caring for yourself*, a caregiver talks to a friend about problems finding time for himself; the other caregiver suggests strategies for dealing with this problem. The list of commonly asked questions provides the selected resources and links related to each question (Figure 2). Each participant in the study can access the website as many or as few times as they wish. At the completion of the 6-week intervention period, researchers at Dalhousie will track the frequency of website use and the most frequently visited components of the website to provide aggregate descriptive information about website use.

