**Figure 2 figure2:**
[figure not shown]
Frequently asked questions for the “caring for yourself” module from the study website.

Participants randomized to the website-coaching group receive (in addition to access to the website) a dose of four personalized coaching sessions (for 6 weeks) from a trained interventionist (licensed independent social worker) who conducts the sessions via videoconference or telephone per each participant’s preference. Completion of these four coaching sessions constitutes a full *dose* of coaching [37]. The four key components of the coaching sessions are (1) session 1—identifying caregivers’ needs for information and support; (2) session 2—strategies for caring for a loved one with multiple sclerosis; (3) session 3—caring for yourself; and (4) session 4—planning and decision-making for the future. The key topics associated with each session are listed in Textbox 1.

Key components of each coaching session.

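### The per-protocol rule requires attendance at coaching that only one arm is offered, so the comparison either has no control group or is selected on adherence in one arm only

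*Protocol article*

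**What the plan says.** The Statistical Methods section announces two analyses: "Intention-to-treat and per-protocol analyses will be conducted". It then fixes who enters the second: "Participants who provide complete data and attend three or more coaching sessions will be included in the per-protocol analysis". The rule is written for participants in general and gives no separate condition for the website-only arm.

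The Setting section restricts coaching to one arm: "coaching via videoconference or telephone (website-coaching group only". The Interventions section agrees: "Participants randomized to the website-coaching group receive (in addition to access to the website) a dose of four personalized coaching sessions". The website is open to both arms with no minimum use: "Each participant in the study can access the website as many or as few times as they wish".

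The model is a between-arm comparison over time: "The linear mixed effects model will include the variables of group assignment, time, and the interaction of time by group". The same approach carries over to the other outcomes: "The analytic approach for the secondary outcomes (anxiety, depression, and negative emotions) will be identical".

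**The concern.** A per-protocol comparison needs an inclusion rule that both arms can meet, or at least one stated for each arm. This rule depends on something that exists in one arm only.

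Caregivers who keep most of their coaching appointments may differ from those who do not, for example in free time, motivation or the course of their distress. Their counterparts in the website-only arm cannot be identified, because nobody there had appointments to keep or miss. Any difference in prognosis between attenders and non-attenders would then appear in the per-protocol result as an effect of coaching. The conclusions are meant to guide refinement and larger-scale testing of the interventions, so a per-protocol result read as evidence for coaching could mislead that decision.

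**Working it through.** **Step 1. Apply the rule to each arm as written.**

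| | Website-coaching | Website-only |
|---|---|---|
| Sessions offered | 4 | 0 |
| Can attend 3 or more? | Yes | No (0 < 3) |
| In the per-protocol set | Attenders with complete data | Nobody |

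With one arm empty, neither the group term nor the group-by-time term can be estimated.

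**Step 2. Apply the session rule to the coaching arm only.**

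| Filter | Website-coaching | Website-only |
|---|---|---|
| Complete data | Yes | Yes |
| Adherence (3 or more of 4 sessions) | Yes | None |

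The controls are therefore not wholly unselected, since they must still provide complete data. The adherence filter works on one side only, and free website use supplies no parallel criterion.

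**Step 3. Illustrate the possible size.** The document states no figure for this, so there is none to reproduce. It gives neither an attendance rate nor a correlation between attendance and outcome; both are assumptions here.

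Let p be the share of the coaching arm attending three or more sessions, and r the correlation between a latent normal tendency to attend and the change in distress. With no treatment effect, the mean among attenders is shifted by

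shift = r × φ(c) / p, where c = Φ⁻¹(1 − p), in SD units of the change.

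- p = 0.7: φ(c)/p = 0.497, so r = 0.1 to 0.3 gives 0.050 to 0.149 SD.
- p = 0.8: φ(c)/p = 0.350, so r = 0.1 to 0.3 gives 0.035 to 0.105 SD.

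Against the planned d of 0.35 (Sample Size section), the extremes are 0.035/0.35 = 10% and 0.149/0.35 = 43%. This treats the two SD scales as the same, which is a further simplification.

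Widening p to 60-90% with the same r gives 0.02 to 0.19 SD, about 6% to 55% of 0.35. The result follows the inputs. A negative r reverses the sign, so the bias could also work against coaching.

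**Step 4. The complete-data condition.** The same section says the mixed model should in most cases account for missing data in the intention-to-treat analysis. The per-protocol rule instead discards caregivers with incomplete data. Planned attrition is 20%, or 0.20 × 150 = 30 caregivers, so this second filter is not trivial.

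**The case against.** The strongest reply is that the empty control arm is a drafting slip. The model has group terms, only one arm has sessions, and the natural reading is complete data in both arms plus three sessions where sessions are offered. One added clause would express that. This is fair, and a reader should not infer that the investigators intend a one-arm analysis. But the clause leads straight to the second reading, where the one-sided selection remains.

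It can also be said that stable differences between attenders and others are largely removed by analysing change from baseline with a participant-specific intercept. That stands: bias requires attendance to be related to change in distress, and the document neither shows nor excludes this. The figures in the working are therefore not evidence that bias is present.

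A reader might infer a contradiction between the three-session rule and the statement that "Completion of these four coaching sessions constitutes a full" dose. The document does not support that. A minimum for inclusion may lie below the full dose, and nowhere is the full dose made the per-protocol condition.

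A reader might also treat the absence of a named primary analysis as an error. That choice is commonly left to a full protocol or analysis plan, which is not at hand, and nothing suggests that per-protocol would override intention-to-treat. Naming intention-to-treat is part of the remedy and not a separate fault.

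Finally, adherence-selected analyses beside intention-to-treat are conventional, and their selection bias is a known limit of interpretation. True, but the rule here is stated explicitly and does not work across the trial's own arms. It is fixed badly and not merely left for later.

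**Conclusion.** The point holds. As written, the rule leaves no comparator; on its sensible reading, it compares coaching attenders having complete data with all website-only caregivers having complete data, which is not a randomised comparison. It applies to distress and to anxiety, depression and negative emotions.

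The logical defect rests only on the document's wording. The size and direction of any bias are unknown, and the 0.035-0.15 SD range is conditional on the assumed attendance and correlation. Severity is moderate: the intention-to-treat analysis does not depend on this rule, per-protocol is not called primary, and the Sample Size section describes the pilot's analyses as exploratory. A reader might infer that the trial's main conclusion is at risk; the document does not support that.

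**What to change.** 1. State that the intention-to-treat analysis decides the comparison for the primary and secondary outcomes.
2. Replace the per-protocol comparison with a complier-average (instrumental-variable) estimate in all randomised caregivers, with assignment as instrument and attendance of coaching as exposure. The website-only arm has no access to coaching, which suits the method.
3. State its assumptions. The exclusion restriction requires that assignment affects outcome only through the chosen exposure. If exposure is three or more sessions, any benefit from one or two sessions would breach it; if exposure is the number of sessions (0-4), the effect per session must be taken as linear.
4. If a per-protocol table is kept, state the criterion for each arm, drop the complete-data condition because the mixed model handles missing visits, and label the table descriptive.

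The cost is wording and one extra analysis. Attendance should be recoverable from the tracked coaching time (Data Collection section) and the interventionists' notes in REDCap (Fidelity section). The downside is precision. With a binary exposure, the estimate is essentially the intention-to-treat effect divided by p, so at the assumed 70-80% attendance its interval is about 1/0.8 = 1.25 to 1/0.7 = 1.43 times as wide as the intention-to-treat interval. Its test adds little to the intention-to-treat test; what it adds is an effect estimate for caregivers who take up coaching.

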## Results

This study was funded in November 2020 by the PCORI. The research protocol was approved by the institutional review board committees of the Case Western Reserve University (January 21, 2021, protocol 20201484) and Dalhousie University (March 23, 2021, protocol 20215484). The study was registered with ClinicalTrials.gov (NCT04662008). Data collection began on April 1, 2021, and as of May 2021, we enrolled 66 participants.

## Discussion

### Principal Findings

There are two main areas of innovation related to this study that add to science. First, caregivers of persons with multiple sclerosis have been the sole focus in only four intervention studies (one was a pilot study), despite the documentation of significant and ongoing needs for strategies to reduce their poor psychological outcomes [5]. This is the first study to examine the effects of a tailored psychoeducational intervention on this vulnerable group of caregivers and will add to the science of caregiving and the evolving science of caregiving of the person with multiple sclerosis.

In addition, this study will test two types of interventions for caregivers of persons with multiple sclerosis. The website-only group intervention represents the delivery of information and support that is self-directed as the person chooses what information is of interest and relevance. However, the website-coaching group enables information and emotional support to be tailored to the caregiver’s needs and allows for professional guidance for skill-building, understanding information, and receipt of emotional support. In addition, although our sample size is not large enough to incorporate many covariates, we will be able to examine the impact of a few caregiver variables (eg, gender, race, and hours of caregiving provided) on the efficacy of the two interventions. This information will guide the refinement of interventions for future testing in a larger study of caregivers of persons with multiple sclerosis.

By examining patterns of use of the website, we will also be able to add to the understanding of the issues and concerns that are of most interest to caregivers of persons with multiple sclerosis. Although previous research has provided some descriptive data [6,8,10], these studies have primarily focused on describing poor psychological outcomes [4,5,14,15], coping strategies [7,9,13], or stressors [6,18,20], identified by caregivers of persons with multiple sclerosis. We will be able to identify topics of most interest (eg, self-care activities) and questions of greatest concern (eg, “How is multiple sclerosis treated?”) elicited directly from website usage of caregivers of persons with multiple sclerosis. This will provide new information and guide recommendations for refining both interventions in preparation for large-scale testing. Similarly, by evaluating aggregated comments from interventionists’ coaching sessions, we will be able to assess issues of greatest concern and topics of greatest interest for caregivers at different points in the trajectory of the illness.

### Conclusions

There remains a lack of data regarding strategies to assist caregivers of persons with multiple sclerosis at different points along the course of illness. Results from this pilot study will determine whether either or both of these interventions provide clinically meaningful improvements in caregivers who are providing care at different points along the caregiving trajectory. Data from this study will provide insights regarding issues of concern for this group of caregivers and guide the refinement and large-scale testing of interventions for this group of vulnerable caregivers.

## Appendix

Multimedia Appendix 1 Fidelity checklist example.

## Abbreviations

HIPAA: Health Insurance Portability and Accountability Act
PCORI: Patient-Centered Outcomes Research Institute
PROMIS: Patient-Reported Outcomes Measurement Information System
REDCap: Research Electronic Data Capture
